## Abstract

**Background:**

Clinical practice guidelines recommend that adults with type 2 diabetes (T2D) sit less and move more throughout the day. The 18-month OPTIMISE Your Health Clinical Trial was developed to support desk-based workers with T2D achieve these recommendations. The two-arm protocol consists of an intervention and control arms. The intervention arm receives 6 months health coaching, a sit-stand desktop workstation and an activity tracker, followed by 6 months of text message support, then 6 months maintenance. The control arm receives a delayed modified intervention after 12 months of usual care. This paper describes the methods of a randomised controlled trial (RCT) evaluating the effectiveness and cost-effectiveness of the intervention, compared to a delayed intervention control.

**Methods:**

This is a two-arm RCT being conducted in Melbourne, Australia. Desk-based workers (≥0.8 full-time equivalent) aged 35–65 years, ambulatory, and with T2D and managed glycaemic control (6.5–10.0% HbA1c), are randomised to the multicomponent intervention (target *n* = 125) or delayed-intervention control (target *n* = 125) conditions. All intervention participants receive 6 months of tailored health coaching assisting them to “sit less” and “move more” at work and throughout the day, supported by a sit-stand desktop workstation and an activity tracker (Fitbit). Participants receive text message-based extended care for a further 6-months (6–12 months) followed by 6-months of non-contact (12–18 months: maintenance). Delayed intervention occurs at 12–18 months for the control arm. Assessments are undertaken at baseline, 3, 6, 12, 15 and 18-months. Primary outcomes are activPAL-measured sitting time (h/16 h day), glycosylated haemoglobin (HbA1c; %, mmol/mol) and, cognitive function measures (visual learning and new memory; Paired Associates Learning Total Errors [adjusted]). Secondary, exploratory, and process outcomes will also be collected throughout the trial.

**Discussion:**

The OPTIMISE Your Health trial will provide unique insights into the benefits of an intervention aimed at sitting less and moving more in desk-bound office workers with T2D, with outcomes relevant to glycaemic control, and to cardiometabolic and brain health. Findings will contribute new insights to add to the evidence base on initiating and maintaining behaviour change with clinical populations and inform practice in diabetes management.

**Trial registration:**

ANZCTRN12618001159246.

**Supplementary Information:**

The online version contains supplementary material available at 10.1186/s12889-022-13123-x.

## Background

Type 2 diabetes (T2D) is a major cause of premature mortality and morbidity due to cardiovascular, renal, ophthalmic and neurological diseases [1]. Adults with T2D have a heightened risk of absenteeism and inability to work, which increases with diabetes duration [2]. For those with T2D, the clustering of chronic conditions, such as cardiovascular disease and dementia, can substantially impact quality of life [3]. Significantly, those with T2D have a 73% increased risk of developing dementia [4]. Diagnosis of T2D is associated with an earlier onset of dementia by an average of 2.5 years, and as such has been identified as a key modifiable risk factor for dementia in later life [5]. Within this context, greater emphasis has been directed to mid-life prevention initiatives in T2D [6]. Optimising glycaemic control is a primary management consideration to reduce and prevent the impact of multiple morbidities [7], including dementia [8].

Participation in regular physical activity is considered a core element for glycaemic control and diabetes management [9]. However, estimates indicate that only one in four adults with T2D achieve the minimum physical activity levels recommended, while one in three with T2D report doing no moderate or vigorous intensity physical activity at all [10]. Furthermore, recent evidence shows that those with T2D can spend some 10 h of their waking hours in sedentary behaviours (sitting, lying or reclining) with low energy expenditure, an amount significantly greater than those without T2D [11]. The detrimental impacts of sedentary behaviour on health are broad [12], including an increased risk of premature mortality [13]. Sedentary time is also associated with poorer glycaemic control in people with T2D [14].

Epidemiological evidence demonstrates that replacing periods of sitting, particularly prolonged sitting time, with stepping is associated with improved glucose and insulin metabolism [15, 16], and lower occurrence of metabolic syndrome [17]. Recent experimental studies in adults with T2D have also shown that interrupting prolonged sitting with frequent short bouts of light-intensity physical activity (e.g., walking, simple resistance or muscle strengthening activities) can lead to substantial reductions in acute post-meal glycaemic responses [18]. In the free-living setting, interrupting sitting time with regular standing or light-intensity activities has resulted in improved 24-h glucose levels compared to engaging in structured exercise alone [19].

To date, controlled intervention trials designed to support adults to reduce their sedentary time have typically targeted the environment (such as through installing sit-stand workstations), the individual (such as through education and prompts), or a combination of both [20]. A recent meta-analysis found that both multicomponent and single-component interventions typically reduced sitting time by 30–60 min per day, predominantly achieved by replacing sitting with standing [21]. Importantly, a dose-response effect has been observed in workplace setting-based interventions, with the higher the exposure to the intervention, the greater the reduction in sitting time, with minimal evidence of either compensation or generalisation outside of the intervention setting [22]. Therefore, initiatives aimed at further reducing time spent sitting and increasing overall physical activity should target behaviours across the whole day, together with consideration of the contexts where the bulk of sitting time occurs (e.g. workplace, domestic).

In addition to understanding such behaviour changes, it is important for intervention trials to evaluate effects of the behaviour change on biological attributes associated with the risks and complications of T2D. The findings of a meta-analysis of interventions targeting sedentary behaviour reductions alone or in combination with increases in physical activity has shown promising, albeit modest, beneficial effects on weight, waist circumference, percent body fat, systolic blood pressure, insulin and HDL levels [23]. However, to date, studies of working age adults have had limited representation of those with clinical conditions such as T2D [23]. Furthermore, there is a paucity of studies intervening for 12 months or more and few have included maintenance evaluations from which to consider sustainability and longer-term effectiveness. As T2D contributes to higher risk for dementia over the lifespan, evaluating maintenance and the potential for long term sustainability of behaviour change is a key consideration.

The OPTIMISE Your Health trial (trial duration – 18 months) is examining the effectiveness of a series of interventions targeting sitting less and moving more across multiple contexts (see footnote). The interventions target behavioural, metabolic and brain health outcomes, and each phase evaluated for cost-effectiveness. The respective interventions are: a 6-month multicomponent intervention; a 6 month extended care intervention; and an abbreviated intervention delivered to delayed intervention controls. This manuscript provides an overview of the OPTIMISE Your Health trial, including the aims, intervention methods and evaluation protocols and contingency with the COVID-19 pandemic.

FOOTNOTE: The OPTIMISE Your Health trial was originally conceived as a 6-month trial inclusive of an intensive sedentary behaviour reduction intervention. By leveraging the merits of the original grant, and seeking to investigate the longer term implications for dementia risk in people with T2D, a second research grant was awarded to the team which allowed for an expanded protocol with extended care to 12 months as well as assessment of maintenaince until 18 months post baseline. Finally, a third research grant was secured to explore an abbreviated intervention: OPTIMISED, to be delivered to delayed intervention control participants at 12–18 months with the aim of informing rapid scale-up. More information is available in electronic supplementary material (Additional file 1).

### Aims and hypotheses

The trial aims to determine the effectiveness, for office workers aged 35–65 years with T2D, of a multi-component intervention with extended care (compared to a control condition, on primary and secondary outcomes.

Secondary aims are to:assess maintenance of outcomes after cessation of study contact (with participants retaining the activity tracker and workstation components only)conduct an economic evaluation to determine the cost effectiveness of the intervention and to estimate the broader social and economic benefits of delaying dementia onset; and,develop and test (in the delayed intervention control arm) a modified version of the intervention suitable for wider-scale implementation (OPTIMISED; the abbreviated form of the intervention).

It is hypothesised (two-tailed) that:The intervention and control group participants will differ in changes in the primary and secondary outcomes (0–6 months)The intervention and control group participants will differ in changes in the primary and secondary outcomes (0–12 months)Changes in primary and secondary outcomes achieved by completion of the intervention will be maintained at 18 months (i.e., no significant 12–18 month change)The OPTIMISE intervention will be cost-effective (measured against the commonly used Australian benchmark of less than $50,000 per quality-adjusted life year gained)The OPTIMISED intervention will be feasible and acceptable (primary) and result in pre-post change (12–18 months) in behaviour for delayed intervention participants.

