### Statistics

#### Sample size

With an estimated 20% attrition based on our previous intervention trials, 2-tailed significance of 2.5% (correcting for two primary outcomes for the original OPTIMISE protocol), 125 participants per group (250 total) are required for 80% power to detect minimum differences of interest in HbA1c and sitting of 0.5% and 0.5 h/16 h-day, assuming standard deviations (SD) of 1.6 and 1.3 and a pre-post correlation (r) of 0.7 and 0.6 respectively. A 0.5% HbA1c decrease is clinically meaningful corresponding to to an approximate 10% reduction in diabetes-related mortality [7]. Assumptions concerning attrition, SD and r for primary and most secondary outcomes were based on Living Well with Diabetes [77], AusDiab [66] and Stand Up Victoria [76] studies. Recruitment projections indicate that a sample of 250 participants is feasible within the allocated timeframe. Recruitment will stop when the trial reaches either the required sample size or the maximum number of participants who can be recruited in the trial’s allotted recruitment timeframe, while complying with the unforeseeable restrictions and conditions related to the COVID-19 pandemic.

The sample size for the cognitive function outcomes are dictated by the original sample size calculations described above. From a sample size of 250, we anticipate 160 participants (80 in each arm) will complete the 12-month assessment. This sample size of 80 per group provides > 80% power (5% 2-tailed significance) to detect our minimum difference of interest in the primary outcome of visual memory (PAL TEA) at 12 months (1/3 SD, d = 0.33) assuming r = 0.7, based on a previous trial [113]. Changes in cognitive function have been detected in a similar sample with 145 participants participating in a 24-week RCT assessing pharmacotherapy to improve metabolic control. Minimum detectable differences will be recalculated if the actual sample size is lower than projected due to the potential impact of the COVID-19 pandemic.

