#### Statistical analyses

Outcomes are all continuous and expected to be either normal or log-normal, in which case log-transformation will be used. Analyses will be performed in STATA version 15 or higher. Significance is set at *p* < 0.05 two-tailed (except for *p* < 0.025 when testing co-primary outcomes based on α = 0.025). To test the differences between groups in primary and secondary outcomes during (3 months), end of the intervention (OPTIMISE; 6 months) and end of the extended maintenance phase (12 months – OPTIMISE-extended) mixed models statistical analysis will be employed, accounting for repeated measures, adjusting for baseline values, randomisation strata, and potential confounders. Within-group changes for intervention participants occurring during the no health coaching contact phase from 12 to 18 months will be tested and compared to intervention phases. Within-group changes will also be tested in the delayed intervention participants receiving the OPTIMISED intervention after 12 months, at the 18 month timepoint, using paired t-tests (or non-parametric paired tests). Possible confounders will be identified a priori from the literature and narrowed down to a number that can be modelled without overfitting, based on an objective criterion not open to manipulation (backwards elimination: retaining age, sex, and *p* < 0.2 association with the outcome). Analyses will follow intention-to-treat principles. Sensitivity to handling missing data will be evaluated by comparing results from the main analyses (evaluable case analysis for mixed models; complete-case analysis for t-tests) with alternative methods that are appropriate for different missing data scenarios (e.g., multiple imputation; selection-covariate adjustment). Descriptive statistics will be used to describe the implementation indicators of the different phases of the intervention.

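### Hypothesis 3 equates maintenance with a non-significant 12–18 month change and sets no margin, so a partial loss of benefit can readily pass as maintained

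*Protocol article*

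**What the plan says.** Aims and hypotheses lists maintenance after study contact ends as the first secondary aim. The third hypothesis makes it operational: changes in the primary and secondary outcomes "will be maintained at 18 months (i.e., no significant 12–18 month change"). The hypotheses are introduced as two-tailed.

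Statistical analyses gives the matching analysis: "Within-group changes for intervention participants occurring during the no health coaching contact phase from 12 to 18 months will be tested". The sentence goes on to say that these changes are also set against the earlier phases: "from 12 to 18 months will be tested and compared to intervention phases". The general test level is "Significance is set at *p* < 0.05 two-tailed", with 0.025 for the co-primary outcomes.

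Neither section states a margin, an equivalence or non-inferiority criterion, or a rule based on a confidence interval. The Sample size section powers between-group contrasts only.

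**The concern.** A test that fails to reject no change does not show that there was no change. When non-significance is the definition of success, the usual incentives reverse. Fewer participants at 18 months, more missing data and noisier measurement all make the favourable conclusion easier to reach, and a large, clean data set with a trivial decline would fail.

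This matters here because 18-month numbers may be thin. The Sample size section expects 80 per arm at 12 months, out of 125 randomised, and allows for a further shortfall from COVID-19. Table 2 marks cognitive testing as dropped during restrictions. The Background calls sustainability of behaviour change a key consideration, so a claim of maintenance will carry weight with readers.

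The rule is stated in the published hypothesis, so this is not a detail left to an analysis plan. A later plan that added a margin would have to depart from the hypothesis as worded.

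**Working it through.** **1. Inputs, all from the Sample size section.** "minimum differences of interest in HbA1c and sitting of 0.5% and 0.5 h/16 h-day"; SD 1.6 with r = 0.7 (HbA1c) and SD 1.3 with r = 0.6 (sitting); PAL TEA 1/3 SD with r = 0.7; 80 per arm expected at 12 months. For the main calculation: "With an estimated 20% attrition based on our previous intervention trials", "125 participants per group (250 total) are required for 80% power", and "2-tailed significance of 2.5" per cent.

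**2. Reproducing the article's own figures.** Baseline-adjusted SD = SD × √(1 − r²).
- HbA1c: 1.6 × √0.51 = 1.143. n = 2 × 1.143² × (2.241 + 0.842)² / 0.5² ≈ 99.3, so 100 per arm; 100/0.8 = 125. This matches.
- Sitting: 1.3 × √0.64 = 1.04, which gives 83 per arm; 83/0.8 ≈ 104, covered by 125.
- PAL TEA: SD √0.51 = 0.714; power at 80 per arm is about 83–84%, consistent with the stated figure of more than 80%.

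So the inputs are read as the authors used them.

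**3. Chance of calling a half-loss maintained.** SD of change = SD × √(2(1 − r)). This assumes that the pre-post r also applies between 12 and 18 months. The probability of a non-significant result comes from a paired t-test (non-central t, two-sided 5%), with non-centrality = loss/(SD of change/√n).
- HbA1c: SD of change 1.6 × √0.6 = 1.239; SE at n = 80 is 0.139; 0.25/0.139 ≈ 1.80; P = 57%.
- Sitting: 1.3 × √0.8 = 1.163; SE 0.130; 0.25/0.130 ≈ 1.92; P = 52%.
- PAL TEA: √0.6 = 0.775; SE 0.087; (1/6)/0.0866 ≈ 1.92; P = 52%.

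**4. Sensitivity.**

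| Scenario | HbA1c | Sitting | PAL TEA |
|---|---|---|---|
| n = 80, stated r | 57% | 52% | 52% |
| n = 100 (20% attrition from 125) | 49% | 43% | 43% |
| n = 64 (assumed further 20% loss from 80) | 64% | 61% | 60% |
| n = 80, r = 0.8 | 41% | 23% | 36% |
| n = 80, stated r, level 0.025 | 68% | 64% | 64% |
| n = 80, loss of the full target | 5% | 3% | 3% |

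A lower correlation moves the figures up: at n = 80, r = 0.6 gives 66% for HbA1c, and r = 0.5 gives 60% for sitting. The article does not say whether the 0.025 level would apply to this contrast.

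**5. The alternative rule.** Suppose maintenance required the one-sided 95% bound to exclude a loss of half the minimum difference. At n = 80 the distance from estimate to bound is 1.664 × SE, or 0.231% (HbA1c), 0.216 h (sitting) and 0.144 SD (PAL TEA). With no true loss, the criterion is met about 56%, 60% and 60% of the time. A true half-loss would pass at most 5% of the time.

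**The case against.** A reader might infer that the plan would declare a half-loss maintained more often than not, without qualification. The documents do not support that. For sitting and PAL TEA the margin over 50% is narrow, and it rests on two inputs. The 80 per arm is the 12-month expectation given for the cognitive outcomes; the 20% attrition planned for HbA1c and sitting implies 100 per arm, and at 100 all three figures fall below 50% at the 5% level. The correlation is stated as pre-post, not for two post-intervention visits, and at 0.8 all three figures are again below 50%. The HbA1c SD matters too: with an assumed SD of 1.4 in place of 1.6, the 57% becomes 47%. These points stand, and the size of the problem must be given as conditional.

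A reader might also infer that significance is the only planned output. It is not, because the change is also to be compared with the intervention phases. That comparison supplies no margin, though, and leaves the wording of the hypothesis as it is.

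Nor would a complete loss of benefit commonly be missed: at 80 participants this happens about 3–5% of the time.

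Finally, a margin of half the minimum difference is not in the documents. It is tied to the planned difference, whereas the hypothesis concerns changes actually achieved. If the achieved benefit were 0.2 h, its complete loss would lie inside a 0.25 h margin. That limits how firmly any one margin can be recommended, but it does not defend the non-significance rule.

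**Conclusion.** The point holds as a flaw in how maintenance is defined. The logical error does not depend on any number. Its size does: a half-loss would be called maintained about 52–57% of the time with 80 participants and the stated correlations, 43–49% with 100, 60–64% with 64, and 23–41% with 80 participants and a correlation of 0.8. These figures use a paired t-test at two-sided 5%; a mixed model could change precision somewhat. Most of them are too high for an error rate behind a positive claim, but they concern partial loss only.

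Maintenance is a secondary aim. The randomised comparisons at 6 and 12 months, the sample size and trial conduct are untouched, so this should be fixed but does not threaten the trial's main conclusions.

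**What to change.** Delete the parenthesis that defines maintenance as the absence of a significant change. Report the 12–18 month and 0–18 month changes in the intervention arm from the mixed model, with confidence intervals. The 0–18 month change shows what benefit remains, which also guards against a margin larger than the benefit achieved.

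Claim maintenance only if the confidence bound for the 12–18 month loss excludes a prespecified loss that the sponsor justifies. Half the minimum difference (0.25% HbA1c, 0.25 h/16 h-day, 1/6 SD PAL TEA) is one example; it is an assumption of this review. If no margin can be agreed, report the estimates and intervals without a verdict on maintenance.

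The cost is a change of wording and one or two model contrasts, with no new data. The drawback is that maintenance becomes harder to claim: with 80 participants and no true loss, the example criterion is met only about 56–60% of the time. That reflects how much information the trial has on this question, which the present rule hides.

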## Methods/design

The Optimise Your Health trial has been iteratively developed over time following the securement of three successive research grants (see supplementary material: Additional file 1). Each grant relates to separate trial phases and interventions with distinct aims, hypotheses, and outcome measures. Recruitment for the original OPTIMISE protocol commenced in June 2019 with 27 participants recruited and completing the 6 month original iteration. In June 2020, recruitment commenced for the extended 18 month trial, which was inclusive of all phases described above. A SPIRIT checklist for standardized protocol items was followed in writing this manuscript (Additional file 11).

### Study design and randomisation

The OPTIMISE Your Health trial is a two-arm individually randomised controlled trial. Randomisation to either the intervention or delayed intervention arm is undertaken in random blocks of sizes 4–8, stratified according to whether participants are taking either 0–1 or 2+ hypoglycaemic medications. Randomisation is automated via REDCap software at the end of the baseline assessment. Due to the nature of the intervention, it is not possible to blind participants or assessors to group assignment.

The trial protocol includes five assessment time-points: baseline, 3- months, 6- months, 12-months, 15- months, and 18- months. Database(s) facilitating intervention management and data collection are undertaken through REDCap — an approved data management platform (version 11.1.25) [24]— with further data stored securely but accessibly to the multidisciplinary multinational research team through The University of Queensland’s Research Data Management System. Ethics approval for both the original and expanded protocols were granted by Alfred Health Human Ethics Committee (Melbourne, Australia), The University of Queensland Institutional Human Research Ethics Committee (Brisbane, Australia), and the University of the Sunshine Coast Human Research Ethics Committee (Sunshine Coast, Australia). The OPTIMISE Your Health trial has been registered with the Australian New Zealand Clinical Trials Registry (ANZCTRN12618001159246; date of registration: 07/03/2018 URL: https://www.anzctr.org.au/Trial/Registration/TrialReview.aspx?id=375487). The trial is undertaken in accordance with CONSORT guidelines (http://www.consort-statement.org/), with Fig. 1 showing the overall study design.

